##### Effect evaluation

After the intervention, differences in the primary outcome “purchase behavior” of students (dependent variable) between the intervention and control group (independent variable) will be analyzed with two-level regression analysis (intention-to-treat). Here, we will correct for correlations of students (level 1) nested within schools (level 2). We will adjust for confounders related to students (e.g., groups of sociodemographic characteristics, behavioral determinants, and environmental determinants). In addition, the moderation effect of gender will be taken into account by stratifying the analyses, based on literature (56). We hypothesize that students in the intervention group will achieve a healthier purchase behavior.

After the intervention period, differences in the secondary outcome “health level” of the canteen between the intervention and control schools will be investigated with descriptive statistics. Thereafter, to gain insight into the effect of the health level of canteens and purchase behavior of students, we will include the health level of canteens in a per protocol analysis. This model will be built similar as the explained intention-to-treat analysis. All information is being gathered with rigor, so these analyses will show which factors make a difference in student behaviors, including implementation features. We hypothesize that intervention schools will improve their health level of the canteen, and that a healthier canteen will lead to healthier purchases. Statistical analyses will be performed using the IBM SPSS statistics version 24.0. MLwiN 2.36 software will be used to conduct the multilevel regression analyses. For all statistical analyses, a two-tailed and 5% significance level will be applied (53).

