Stakeholders need support to implement the guidelines in their school (15, 26, 27). Such an implementation support plan will be better aligned to the needs of practice, and thereby more feasible, if the needs and wishes of stakeholders are taken into account (9, 28, 29). Therefore, during the development and evaluation stage, collaboration with these stakeholders is recommended (28, 29). It is also recommended to apply theory, such as the use of a structural framework for the development and evaluation of the implementation plan, the use of behavior change models to translate the need of practice into implementation strategies and the use of a combination of implementation tools (30, 31). The collaboration with practice in combination with the use of theory will increase the likelihood of a feasible and effective implementation. To succeed over time, implementation of new guidelines should allow adaptations to local circumstances but, nonetheless, be conducted with rigor and consistency. This article describes: (1) how we developed a plan to support implementation of canteen guidelines in Dutch secondary schools; and (2) how we will evaluate this implementation plan on process and effect level. The process will be evaluated on factors affecting implementation perceived by stakeholders and the quality of implementation. The effect will be evaluated by determining changes in the health level of canteens and in the self-reported purchase behavior of adolescents.

The input of practice during the development and evaluation of our implementation plan will give insights to researchers about working elements. We hypothesize that this approach will increase future uptake and effect of the implementation plan. With our implementation plan we aim to facilitate the process to create a healthier school canteen, and thereby to stimulate Dutch adolescents to purchase healthier foods and beverages during school time.

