### Evaluation of the Implementation Plan on Process and Effect Level

#### Setting and Study Design

To evaluate both the process and effect of the developed implementation plan, a 6-month quasi-experimental controlled design will be used with 10 intervention and 10 matched control schools (see Figure 2). The included schools will have a variety of characteristics, so the results can be translated to other Dutch schools. Control schools will be matched by the main characteristics: how the catering is provided (i.e., by a catering company, or the school itself), school size (<1,000 and ≥1,000 students), level of secondary education (vocational, senior general, and pre-university), availability of (many) shops near the school, and whether or not the school has a policy for students to stay on the schoolyard during breaks. Intervention schools will receive the developed implementation plan to support implementation of the Guidelines for Healthier Canteens, whereas the control schools will receive the guidelines only. Control schools will receive these guidelines in a short meeting and on paper after the baseline measurements. After the intervention period, control schools will receive the intervention. This quasi-experimental study will be carried out according to: (1) the project application (Nr: 50-53100-98-043, date: 2 December 2014) approved by funding organization ZonMw, (2) the study protocol approved by the VU University Medical Centre (WC2015-008 and 2015.331), and (3) registration in the Dutch Trial Register (NTR5922).

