**Effect evaluation measures**			
**Questionnaire purchase behavior and determinants of purchase behavior of students (measured at T0 and T2)**			
Demographics	Frequencies, multiple choice	Age, gender, education level	What is your current age?
Purchase behavior of foods and drinks	Frequencies	In school at the counter In school at vending machines	How often per week do you buy fruits at the school counter?
Behavioral determinants of healthy purchase behavior at school	5-point Likert scale	Attitude Perceived behavioral control Subjective norm	Next month, I intend to buy healthier products in the school canteen
Environmental determinants of healthy eating behavior during school time	Multiple choice	Breakfast behavior Money spending at school Food and drinks brought from home Food and drinks bought outside school	I bring foods to school (0–>5) times a week

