##### Effect evaluation

The effectiveness of the implementation process will be evaluated by measuring at baseline and at follow-up after 6 months via (1) the self-reported purchase behavior of students, and (2) the “health level” of the school canteen (Table 2).

The questionnaire to assess the primary outcome self-reported purchase behavior of students, the behavioral determinants of purchase behavior (Perceived behavioral control, attitude, and subjective norm of healthy eating in school) and the environmental determinants (like food brought from home, purchases during but outside school) is derived from existing validated Dutch questionnaires (45–49). The frequency of food/beverage purchases per week in the school canteen/vending machines of products that are the “healthier products” and products which should be consumed only occasionally, will be asked (21, 50). The questionnaire will be reviewed and discussed on face validity and content validity by all project members involved. Thereafter, it will be pretested by respondents of the same age as the target group using the cognitive interview method think-aloud (51). The aim of this pretest is to get insight into respondents' comprehensibility and the length of the questionnaire, to be able to adapt questions if needed (51). The questionnaire will be administered digitally in a classroom setting in the presence of a teacher or researcher.

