#### Statistical Analysis

##### Process evaluation

To test for differences in factors affecting implementation perceived by stakeholders (dependent variable) between the intervention and control group (independent variable) after the intervention (6 months), linear two-level regression analysis will be used. The used levels will be: stakeholders (level 1) and schools (level 2) and we will adjust for baseline measurements. This analysis will be performed for each individual (e.g., knowledge, attitude, and self-efficacy) and environmental factor (e.g., need for support, innovation). When these analyses show no significant difference between school variance, a linear regression analysis will be performed (53). We hypothesize that the stakeholders in the intervention group will positively change their perceived factors due to the support in implementation.

To investigate the quality of implementation quantitatively (dose delivered, dose received, and satisfaction) of each implementation tool, descriptive statistics will be used. This information will be complemented by qualitative data about the overall experiences of stakeholders. This data will be analyzed in three rounds, following the thematic content approach (36). First, answers will be labeled with descriptive codes. Second, the codes will be split or merged and interpretative codes will be created. Third, codes will be compared and overarching themes defined.

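### The primary effect analysis compares purchases at follow-up without stating adjustment for baseline purchases, although schools are not randomised and the baseline value is collected

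*Protocol article*

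**What the plan says.** Under Setting and Study Design, the article describes "a 6-month quasi-experimental controlled design will be used with 10 intervention and 10 matched control schools". The matching factors are school features: "Control schools will be matched by the main characteristics: how the catering is provided", followed by school size, education level, shops nearby and the rule on staying on the schoolyard. Purchase behaviour is not a matching factor.

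The Introduction sets the aim in terms of change: "The effect will be evaluated by determining changes in the health level of canteens and in the self-reported purchase behavior of adolescents". Outcomes, Effect evaluation, says that effectiveness "will be evaluated by measuring at baseline and at follow-up after 6 months via (1) the self-reported purchase behavior of students". Table 2 confirms the timing: "Questionnaire purchase behavior and determinants of purchase behavior of students (measured at T0 and T2"). That table lists purchase behaviour, behavioural determinants and environmental determinants as separate measures.

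Statistical Analysis, Effect evaluation, then compares the arms after the intervention with students nested in schools, and gives the covariates as: "We will adjust for confounders related to students (e.g., groups of sociodemographic characteristics, behavioral determinants, and environmental determinants"). For the process outcomes, the paragraph on the equivalent two-level comparison says: "The used levels will be: stakeholders (level 1) and schools (level 2) and we will adjust for baseline measurements".

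**The concern.** In a non-randomised comparison of 10 schools with 10 others, the baseline value of the outcome is usually the most informative covariate. It captures pre-existing differences in what students buy that school-level matching may miss, and it removes outcome variance that would otherwise sit in the standard error. The plan collects this value and sets an aim of determining change, but the primary model states no use for it.

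Two things are at stake. A difference between the arms that existed before the intervention could be read as an effect, or could mask one. And precision already paid for through the T0 questionnaire would go unused.

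A related gap concerns the covariates that are named. Attitude, perceived control, subjective norm, money spent at school and purchases outside school are asked at T0 and T2. The intervention could change them. If T2 values were used, part of the intervention effect could be adjusted away.

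**Working it through.** **Does any named covariate group contain T0 purchases?** Three groups are named: sociodemographic characteristics, behavioural determinants and environmental determinants. Table 2 lists purchase behaviour in school as a measure apart from all three. Its environmental determinants include food bought outside school, which is a different quantity. So none of the named groups contains the baseline value of the primary outcome.

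**Process model against effect model**

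| | Process analysis | Primary effect analysis |
|---|---|---|
| Contrast | arms after 6 months | arms after the intervention |
| Levels | stakeholders in schools | students in schools |
| Outcome measured at baseline | yes | yes |
| Baseline adjustment stated | yes | no |

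**The plan's own figures.** The article quantifies nothing on this point. The sample size section supplies the ICC of 0.05, the 10% difference (read here as 10 percentage points) and 1,505 students in 20 schools, so 1,505/20 = 75.25 per school. It gives no control proportion. The 1,505 is not in dispute here.

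**Carry-over of a baseline gap.** Bias = slope × gap, where the slope is the regression of follow-up on baseline purchases. The slope is not in the document; 0.3 to 0.9 is assumed.

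- 5-point gap: 0.3 × 5 = 1.5 to 0.9 × 5 = 4.5 points, or 15% to 45% of the 10-point target.
- 10-point gap: 3 to 9 points, or 30% to 90%.

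These are figures before any absorption by matching or by the other covariates.

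**How large a gap chance alone could produce.** Ignoring matching, with 75 students per school,
SD of arm difference = √[(2/10) × p(1−p) × (0.05 + 0.95/75)].

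- p = 0.2: √(0.2 × 0.16 × 0.0627) = 4.5 points.
- p = 0.5: √(0.2 × 0.25 × 0.0627) = 5.6 points.

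Under a normal distribution a gap above 5 points has probability 26% (p = 0.2) to 37% (p = 0.5). With the 100 students per school planned at recruitment, the SDs are 4.4 and 5.5 points and the probabilities 25% and 36%. This shows that gaps of the size used above are plausible. It is not a probability of bias.

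**Precision, as an illustration.** Let rₛ be the baseline-to-follow-up correlation between schools and rᵢ that within students (both assumed).
Variance ratio = [0.05(1−rₛ²) + 0.95(1−rᵢ²)/75] / [0.05 + 0.95/75].

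- rₛ = 0.5, rᵢ = 0.4: 0.77
- rₛ = 0.6, rᵢ = 0.5: 0.66
- rₛ = 0.8, rᵢ = 0.5: 0.44

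So variance falls by 23% to 56%. The formula takes both correlations as fully used, which in general needs the school T0 mean in the model as well as the student value.

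For power, SE² = [p₁(1−p₁) + p₂(1−p₂)]/10 × 0.0627 × variance ratio, tested with t on 18 df:

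- 50% against 60%: SE = 5.5 points and power 40% unadjusted; about 50% to 73% adjusted.
- 6.6% against 16.6% (where the standard two-proportion formula times the design effect comes close to the stated sample size, at 1,508): SE = 3.5 points and power 76% unadjusted; about 86% to 98% adjusted.

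The direction is the same in both, but the size depends on the unstated control proportion and the assumed correlations.

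**The case against.** The strongest reply is that the text leaves the matter open. The covariate list is given by example, the Introduction speaks of changes, and the Outcomes section refers to measurement at baseline and follow-up; all of this is compatible with a model that includes T0 purchases. The article also condenses an approved study protocol that is not shown, where a full covariate list could stand. Much of this holds. A reader might infer that the authors have decided against baseline adjustment; the document does not say so. What remains is that the article does specify baseline adjustment for the process outcomes and not for the primary outcome. That contrast takes the point beyond ordinary condensation.

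Three further inferences also go too far:

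- **That a baseline gap passes in full into the estimate.** It carries over in proportion to the slope. Matching on catering, size, education level, shops and schoolyard policy, together with the listed covariates, may absorb part of it.
- **That the 26% to 37% figure is a risk of bias.** It describes chance imbalance without matching. The two-level standard error already reflects between-school variation, so chance imbalance costs precision. Systematic differences from non-random allocation are what would bias the estimate, and the document gives no basis for their size.
- **That T2 values of the determinants will be adjusted for.** No section says so, and calling these variables confounders points the other way. The time point is simply not stated.

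**Conclusion.** The point holds as a gap in the specification of the primary model. The article sets out a follow-up comparison between non-randomised arms and does not commit to adjusting for baseline purchases, while committing to the equivalent adjustment for the process outcomes. It also leaves open when the behavioural and environmental covariates are measured.

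The size is conditional. At assumed slopes of 0.3 to 0.9, each 5 points of baseline gap would bring at most 1.5 to 4.5 points of bias, before matching and other covariates take their share. Whether such a gap will arise cannot be known from the document. The variance and power gains are illustrations under assumed correlations and control proportions; they support the direction of the change but not a particular number. Baseline adjustment would reduce confounding by prior purchase behaviour. It would not make the comparison equivalent to a randomised one.

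**What to change.** In Statistical Analysis, Effect evaluation, state that the primary two-level model includes the student's T0 purchase behaviour as a covariate, and that all other student covariates, including the behavioural and environmental determinants, are taken from T0.

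Two optional additions: the school's T0 mean purchase behaviour, which allows the between-school slope to differ from the within-student slope; and a difference-in-change estimate as a sensitivity analysis, since the groups are not randomised.

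The cost is one or two sentences. Students already complete the questionnaire at both times, so no new data are needed. The wording should be settled before follow-up outcomes are compared by arm, so that the choice of covariates does not depend on the results.

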#### Sample Size

The power calculation was based on the primary outcome, i.e., the self-reported purchase behavior of healthier products per week. In this calculation we included an 80% power and a 5% significance level (53). To detect a 10% difference in the proportion of purchasing healthier vs. unhealthier products per week (dichotomous variable) between the intervention and control group, with the expected multi-level structure between schools (correlation of 0.05 between schools), and to obtain sufficient power (80%), we calculated that 1,505 students spread among 10 intervention and 10 control schools are needed. The increase of 10% in purchase behavior of healthier products is based on results of comparable studies in schools (54). Consequently, we aimed to recruit 20 schools and 100 students per school, based on an expected dropout rate of 10% (55).

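### Gender moderation is to be assessed by stratified analyses, which give two estimates but no test or interval for their difference; an arm-by-gender interaction is needed

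*Protocol article*

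**What the plan says.** In the protocol article, under Statistical Analysis, Effect evaluation, the primary outcome (students' purchase behaviour) is compared between arms after the intervention and "will be analyzed with two-level regression analysis (intention-to-treat"). For clustering, "we will correct for correlations of students (level 1) nested within schools (level 2"). After a sentence on confounders comes the one at issue, introduced as an addition: "the moderation effect of gender will be taken into account by stratifying the analyses, based on literature (56"). No arm-by-gender term is named, and no rule is given for comparing the two strata. At the end of the subsection: "For all statistical analyses, a two-tailed and 5% significance level will be applied (53").

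The Sample Size section concerns the whole-group comparison only. Its target is "To detect a 10% difference in the proportion of purchasing healthier vs. unhealthier products per week (dichotomous variable"), with 80% power and a "correlation of 0.05 between schools", which leads to 1,505 students in 10 + 10 schools. It says nothing about power by gender or for an interaction.

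**The concern.** The stated question is whether gender modifies the intervention effect. The stated method is to analyse boys and girls separately. The two do not match: the quantity of interest is the difference between the two gender-specific effects, and no model in the plan contains it.

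Without a test or interval for that difference, readers tend to compare p-values. A result that is significant in girls and not in boys, or the reverse, then looks like moderation. That pattern arises often by chance when the true effects are equal, and it would bear on a prespecified subgroup statement about the primary outcome.

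**Working it through.** **Inputs.** From the Sample Size section: 1,505 students, 20 schools, ICC 0.05, two-sided 5%, 80% power, a 10% difference (read as 10 percentage points), and 2,000 recruited with 10% dropout, which leaves 1,800. Not given, so assumed: gender split 50:50 (40:60 also tried), both genders in every school, equal school sizes, and a baseline proportion varied from 6.5% to 50%.

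**1. The plan's own figure.** Students per school: 1,505/20 = 75.25. Design effect = 1 + (75.25 − 1) × 0.05 = 4.71. Effective sample size = 1,505/4.71 ≈ 319. For 6.5% vs 16.5%, the two-proportion formula needs 318 independent students, and 318 × 4.71 ≈ 1,499, close to 1,505. For 20% vs 30% it needs 588, or about 2,771 after inflation. So 1,505 fits only a low baseline (or its mirror image near 100%). The baseline is not stated, so the figure can be neither confirmed nor refuted, and a range is used below.

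**2. How often the strata disagree by chance, calibrated to the plan's 80%.** Students per gender per school: 37.6. Design effect = 1 + 36.6 × 0.05 = 2.83. Effective size per gender = 752.5/2.83 ≈ 266.
- Power per gender = Φ(2.80 × √(266/319) − 1.96) = Φ(0.60) ≈ 72%.
- Correlation of the two estimates under a shared school effect = 0.05/(0.05 + 0.95/37.6) ≈ 0.66.
- With that correlation both genders are significant in 61.4% of trials and exactly one in about 22%.

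**3. Simulation over the unstated baseline.** 100,000 trials per row, 37 per gender per school, shared school effect, t on 18 df, the same 10-point effect in both genders:

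| Baseline vs intervention | Power per gender | Exactly one gender significant | Interaction test rejects |
|---|---|---|---|
| 6.5% vs 16.5% | 69% | 25% | about 5% |
| 20% vs 30% | 43% | 28% | about 5% |
| 50% vs 60% | 34% | 26% | about 5% |

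With 45 per gender per school (1,800 students), exactly one is significant in 22–24% at the two extreme baselines. The overall range is therefore about 22–28%.

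**4. What an interaction test can deliver** (N = 1,505, calibrated as in step 2). Relative variances:
- pooled effect: 0.05 + 0.95/75.25 = 0.0626
- interaction, shared school effect: 2 × 0.95/37.6 = 0.0505
- interaction, school effects independent by gender: 2 × (0.05 + 0.95/37.6) = 0.1505

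For a 10-point difference between genders, power is Φ(2.80 × √(0.0626/0.0505) − 1.96) ≈ 88% with a shared school effect, and Φ(2.80 × √(0.0626/0.1505) − 1.96) ≈ 44% with independent effects. For a 5-point difference the figures are about 35% and 15%.

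**5. What stratifying costs in power.** Calibrated to the plan, 80% overall becomes 72% per gender at 1,505 students, and 81% becomes 75% at 1,800. At an assumed 50% baseline, 39% overall becomes 34%. The loss is about 5–8 points because clustering, not the number of students, dominates the variance. For a stratum holding only 40% of 1,505 students, power is 69%.

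**The case against.** **The strata do not replace the primary result.** A reader might infer that they do, leaving the pooled comparison unreported. The text does not support this. The gender sentence is introduced as an addition to the intention-to-treat comparison, the hypothesis that follows concerns intervention students as a whole, and the trial is sized for the whole group. What remains is loose wording: the sentence does not say which analyses are stratified or that the pooled one stays primary.

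**Stratifying is not what makes power low.** The 34% per gender at a 50% baseline is tempting to cite, but pooled power there is itself only about 40%, and that baseline is assumed.

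**The chance of a false positive in at least one gender** (about 8.5% with no effect) matters only if significance in either gender counts as success. The plan has no such rule, so the error rate of the primary test is not inflated.

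**The remedy has limits.** The interaction escapes the ICC only if boys and girls share the school effect. Otherwise its power roughly halves.

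**An article condenses.** Exact model terms may be left to a fuller document, and gender was chosen in advance from the literature. This carries some weight, but the article does not leave the method open: it names one, and that one does not answer the question posed.

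**Conclusion.** The point holds in a limited form. Stratifying gives gender-specific estimates but no inference about their difference, so it does not assess moderation. If the effect is the same in both genders, about 22–28% of trials would show significance in exactly one of them, against about 5% in which an interaction test would err. This range is stable over baselines of 6.5–50% and 37–45 students per gender per school. It rests on a 50:50 split, ICC 0.05, equal school sizes, a 10-point effect and a school effect shared by boys and girls.

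The documents support neither a claim that the primary result is lost nor one that stratifying severely weakens the trial. The defect affects how a moderation analysis will be read, not the validity of the main comparison.

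**What to change.** - State that the pooled two-level intention-to-treat comparison is the primary analysis.
- Assess moderation by adding gender and arm × gender to that model, and report the interaction with its 95% confidence interval.
- Allow a school-by-gender random effect. Without it, the precision of the interaction rests on boys and girls sharing the school effect.
- Give gender-specific estimates with confidence intervals as supportive results, with no claim of moderation from one p-value falling below 5% and the other not.
- State that power for the interaction is limited and that a non-significant interaction does not show equal effects.

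The cost is a few lines of analysis text. Gender is already collected in the student questionnaire, and no further students or schools are needed. The one drawback is a possibly wide interval for the interaction, but that shows honestly what the data can say.
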